#### Subsequent study visits

##### Adherence assessment

Fortnightly ‘home visits’ by experienced research assistants to the participants’ homes in the community are done to assess the following: (1) documentation of episodes of infection (rate, days affected), (2) recording any adverse events/effects, (3) documentation of details of unplanned hospital and healthcare facility attendance, for example, to a doctor, traditional healer, clinic or hospital, (4) provision of educational information to participants on the correct use of the study interventions and encouraging adherence to study interventions, (5) adherence monitoring (measured from parental questioning along with assessment of residual MNPs and syrup) and (6) advice on future visits.

##### Monthly DP issuance

The research assistants issue the investigational products monthly during a home visit. The following activities (including data collection) are undertaken: issuance of the study interventions according to study protocol and adherence monitoring (measured from parental questioning along with assessment of residual MNPs and syrup). In addition, unused investigational products are collected.

##### Study midline visit (at 12 months of age (-2 weeks or +6 weeks))

The participating child and their parent/legal guardian attend the health facility at the end of the 6 months intervention for developmental assessments using locally adapted Bayley Scales of Infant and Toddler Development, Wolke’s Behavioural Rating (WBR) and Child Temperament using the Bates’ Infant Characteristics Questionnaire. Anthropometric measurements are conducted on both the child and the mother. Venous blood (3 mL) for Hb testing, determination of iron indices, malaria microscopy (to be conducted at the completion of the trial) and malaria filter paper for future PCR analyses is collected from the child.

##### Monthly malaria infection testing

Research assistants visit the homes of participants once per month after completion of the midline visit for assessment of episodes of infection (rate, number of days affected) in the previous 1 month and documentation of unplanned hospital and/or healthcare facility attendance (details of any interim visit to doctor, clinical or hospital visits in the previous month) and record of healthcare usage.

##### Endline visit (at 18 months of age (−2 weeks or +6 weeks))

The procedures are similar to the midline visit described above and in online supplemental file 2.

##### Unscheduled visits

Mothers or legal guardians are asked to attend the research site/clinic when their child is symptomatically unwell. They are managed according to national standard treatment guidelines by a trained healthcare provider. Blood samples for malaria rapid diagnostic test (mRDT) and blood culture are taken if clinically indicated. The clinical diagnosis of the unscheduled visit is recorded in the participant’s record and captured on the study’s interim visit case report form (CRF) and adverse event form. If the child requires inpatient care, they are referred to the Chikwawa district hospital.

### Laboratory procedures

A capillary blood sample is collected by finger prick from all age-eligible participants to measure the Hb concentration by HemoCue (HemoCue 301+, Angelholm, Sweden) and *Plasmodium* infection by RDT (mRDTs); (SD Bioline Malaria Ag Pf/Pan, Standard Diagnostics) at baseline. In addition, up to 3 mL venous blood sample is collected from all enrolled participants at baseline, midline, endline and unscheduled visits (if necessary) for Hb testing, determination of iron indices (serum – for ferritin, CRP and AGP), thick and thin malaria slides for malaria microscopy testing and filter paper for *Plasmodium* PCR. Families are encouraged to permit the collection of venous blood for venous Hb and iron and inflammation biomarkers at all time points; however, if a family refuses venous blood collection or if collection was unsuccessful, data for the primary outcome and other non-laboratory secondary outcomes will still be collected.

### Data Safety and Monitoring Committee

An independent Data Safety and Monitoring Committee (DSMC) comprised of international experts in clinical trials, child health, infectious diseases, epidemiology and statistics was set-up to review regularly, safety data of the ongoing trial. The DSMC may recommend to the sponsor and investigators whether to continue, modify or terminate the trial on ethical grounds.

### Outcomes

#### The primary outcome

Cognitive development: assessed by the differences in Bayley-III Cognitive Composite Score (CogCS) between intervention arms measured after 6 months intervention (midline) and 12 months post-intervention (endline). The Bayley-III is a validated index of child development that can be administered in ~0.5–1 hour and comprises cognitive, motor and language development scales. Assessors are specially trained to administer the tests, and inter-rater reliability is established before starting data collection. In addition, we perform 10% interobserver testing to monitor inter-rater reliability of the measure over the study period.

#### Secondary outcomes

Secondary outcomes include: motor and language development assessed by Bayley-III Motor (MotCS) and Language (LangCS) Composite Scores (+6 months, +12 months), behaviour assessed by WBR, temperament, growth assessed by weight-for-age z-score, length-for-age z-score, weight-for-length z-score, head circumference z-score, anaemia (Hb<11 g/dL), Hb concentration, iron deficiency (ferritin <12 ng/µL adjusted for inflammation assessed by CRP or AGP), ferritin concentration and iron deficiency anaemia.

Safety will be assessed by prevalence of malaria parasitaemia and CRP and inflammation (CRP>5 mg/L) at the end of the intervention and a further 6 months post-intervention; episodes of caregiver reported symptoms (eg, fever, diarrhoea, vomiting, cough) determined by the biweekly and monthly morbidity questionnaire; episodes of unplanned clinical visits and hospitalisations and deaths.

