## Objectives

The primary objective is to determine (1) if the efficacy of iron supplements or MNPs (containing iron) given with malaria chemoprevention is superior to malaria chemoprevention alone, or (2) if the efficacy of malaria chemoprevention alone is superior to placebo, on child cognitive development (measured using locally adapted Bayley Scales of Infant and Toddler Development third edition (Bayley-III) Cognitive Composite Scores^39^ at the end of the 6-month intervention period.

The specific objectives are:

Determine if the efficacy of (a) iron (as supplements or MNPs) given with malaria chemoprevention is superior to malaria chemoprevention alone or (b) if the efficacy of malaria chemoprevention alone is superior to placebo on.Child cognitive development, child motor, language, behavioural development, temperament and physical growth at the end of the 6 months intervention and a further 6 months post-intervention.Anaemia (and haemoglobin concentration), iron deficiency (and ferritin) and iron deficiency anaemia after 6 months of intervention and 6 months post-intervention.Compare the effects of iron given as supplements to MNPs on the above outcomes after 6 months of intervention and a further 6 months post-intervention.Determine the safety of iron (as supplements or MNPs) given with malaria chemoprevention on the risk of malaria and other morbidities versus malaria chemoprevention alone or placebo during and post-intervention.Determine the efficacy of malaria chemoprevention alone compared with placebo on clinical malaria, parasitaemia and malaria-specific clinical visits and all-cause sick visits during and after intervention.Determine the safety of iron (as supplements or MNPs) given with malaria chemoprevention compared with placebo on infection risk in young children, during and post-intervention.

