##### Baseline and enrolment (at 6 months of age (±14 days))

A second, more detailed consent form for participation in the study is signed, and a study identification number is assigned. Randomisation is performed after the following baseline evaluations (see online supplemental file 2) are carried out and necessary information collected: demographic information, socioeconomic status (using the Malawi Demographic Health Survey standard of living scale), medical history, family care indicators^43^/index, feelings questionnaire,^44^ cost survey (household out of pocket healthcare costs), food security questionnaire,^45^ dietary diversity questionnaire,^46^ developmental screening using Caregiver Reported Early Development Instrument (CREDI),^47^ anthropometric measurements (weight, length, MUAC and head circumference) and anthropometric measurements for the mother (weight, height). A venous blood sample (3 mL), for Hb testing, determination of iron indices (serum – for ferritin, C reactive protein (CRP) and Arabinogalactan protein (AGP)), thick and thin malaria slides for malaria microscopy testing (to be conducted at the completion of the trial) and filter paper for plasmodium PCR, is collected from the child. The mother is given educational information regarding the use of study medications, administration of the first dose of DP and instructions on how to administer day 2 and day 3 DP treatments, administration of the first dose of iron syrup, use of MNPs and advice on future visits.

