### Statistical analysis plan

A stand-alone statistical analysis plan will be detailed before breaking the blind. This plan will detail all principles and precise methods of analysis, including primary and secondary treatment effects of interest; alternative analyses if model assumptions do not hold; and additional analyses. Participants will be analysed according to their randomised treatment group for efficacy objectives and actual treatment group for safety objectives. The primary outcome of Bayley-III CogCS will be analysed using a mixed-model repeated measures analysis including in the model treatment group, time point and group by time point interaction. The stratification variables sex and site will be included in all models as main effects. In addition, the CREDI variable (collected at baseline) will be included as a main effect in the models for childhood development as it is considered prognostic for childhood development outcomes. Secondary repeated continuous outcomes (eg, growth outcomes) will be analysed similarly to Bayley-III CogCS. The outcome may be appropriately transformed before fitting the analysis model if considered skewed (eg, log-transformation for ferritin). Secondary repeated binary outcomes (eg, haematological outcomes) will be analysed using a log-binomial model and account for the repeated measures with a random intercept for participants. Safety (eg, AEs, infections, hospital attendance) will be summarised during the intervention and post-intervention periods separately and compared between the groups. Analysis of binary repeated outcome safety data (eg, inflammation) and continuous repeated outcome safety data (eg, CRP) will be analysed similarly to the secondary outcomes detailed above. Episode safety data (eg, caregiver reported diarrhoea episodes) will be analysed using negative binomial regression models. Subgroup analyses (eg, sex, site, iron deficiency) will be performed to explore the heterogeneity of the results independent of the study findings.

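### The ferritin cut-off for iron deficiency is printed in ng/µL, 1000 times the ng/mL value evidently meant; taken literally, practically every child is iron deficient

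*Protocol article*

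**What the plan says.** The protocol article, under Outcomes, Secondary outcomes, lists among the haematological outcomes "anaemia (Hb<11 g/dL), Hb concentration", then "iron deficiency (ferritin <12 ng/µL adjusted for inflammation assessed by CRP or AGP", then "ferritin concentration and iron deficiency anaemia". This is the only place where a ferritin cut-off or a ferritin unit appears.

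Three other statements depend on it or may do so:

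- Objectives names "iron deficiency (and ferritin) and iron deficiency anaemia after 6 months of intervention and 6 months post-intervention" among the endpoints to be compared.
- Statistical analysis plan: "Secondary repeated binary outcomes (eg, haematological outcomes) will be analysed using a log-binomial model", with a random intercept for participant.
- Statistical analysis plan: "Subgroup analyses (eg, sex, site, iron deficiency) will be performed to explore the heterogeneity of the results". No separate definition of iron deficiency is given there.

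The section on baseline and enrolment expands the two inflammation markers as "C reactive protein (CRP) and Arabinogalactan protein (AGP".

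**The concern.** The cut-off is what turns a measured ferritin value into a yes/no outcome. If the printed unit is out by a factor of 1000, the classification no longer separates children. At stake are the binary iron-deficiency outcome at both time points, the distinct meaning of iron deficiency anaemia, and any subgroup analysis that uses the same definition. The unit does not look like a text-reading fault: g/dL and mg/L are printed normally in the same section, and mL is printed normally for the venous blood volumes.

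**Working it through.** **Nothing to reproduce.** The cut-off is a definition and the article gives no derivation for it. The check is a unit conversion, followed by its effect on classification.

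**1. Conversion.** 12 ng/µL × 1000 µL/mL = 12,000 ng/mL = 12,000 µg/L. By comparison, 12 ng/mL = 12 µg/L. The ratio is 12,000 / 12 = 1000.

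**2. Share of children below each cut-off.** The article gives no ferritin mean, SD or range, so a distribution has to be assumed. I take the value compared with the cut-off as log-normal with geometric mean GM and log-SD s:

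P(ferritin < c) = Φ((ln c − ln GM) / s)

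The log-SD runs over 0.7, 1.0 and 1.3. The number of children is the planned total of 2168.

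| GM (µg/L), assumed | Lowest P(<12,000 µg/L) over s | Most children above 12,000 µg/L, of 2168 | P(<12 µg/L) over s |
|---|---|---|---|
| 10 | 0.99999998 | 0.00005 | 0.556–0.603 |
| 20 | 0.99999957 | 0.00093 | 0.233–0.347 |
| 35 | 0.99999644 | 0.0077 | 0.063–0.205 |
| 100 | 0.99988461 | 0.25 | 0.001–0.051 |
| 300 (extreme) | 0.99772729 | 4.9 | 0.000–0.007 |

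Example, GM 100 and s 1.3: ln(12,000/100)/1.3 = 4.787/1.3 = 3.68. Φ(3.68) is about 0.99988, and 2168 × 0.000115 = 0.25 children.

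Over GM 10–100, a cut-off of 12 µg/L classifies between about 0.1% and 60% as deficient. The printed one classifies at least 99.98% as deficient.

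**3. Iron deficiency as an outcome.** If prevalence in every arm lies between 0.99988 and 1, the risk ratio between any two arms lies between 0.99988 and 1/0.99988 = 1.00012. Allowing the extreme case, it lies between 0.9977 and 1/0.9977 = 1.0023. The log-binomial model has nothing to estimate.

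**4. Subgroup.** With the same definition, the not-deficient stratum is expected to hold at most 0.25 of 2168 children over GM 10–100, and about 5 in the extreme case.

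**5. Iron deficiency anaemia.** I take this as Hb <11 g/dL together with iron deficiency, since the article does not spell it out. Its prevalence can then fall short of anaemia prevalence by at most 1 − 0.99988 = 0.012 percentage points (0.23 in the extreme case). It becomes a copy of anaemia and can still differ between arms.

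**6. What the article itself implies.** The introductory section on anaemia in malaria-endemic areas cites a study with 61.2% of children anaemic but 13% with iron deficiency anaemia. Under a cut-off that nearly every child falls below, the second figure would have to be almost equal to the first. The introduction also contrasts iron-deficient with iron-replete children, and the Discussion describes a prevalence that peaks at 9–12 months and then falls. The literal cut-off therefore cannot be what the authors mean.

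**The case against.** The best defence is that this is a misprint with little practical reach. To do harm, someone would have to convert laboratory values to ng/µL, or the cut-off to 12,000 µg/L, and then accept a prevalence near 100% in every arm. The article promises a stand-alone analysis plan before unblinding. Neither that plan nor the full protocol is shown, and nothing indicates that they repeat the unit. The subgroup is only an example in an exploratory list, without its own cut-off. All of this stands and limits the severity. It does not remove the point, because the article states a defining threshold wrongly and nothing else in it supplies the right one.

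A reader might infer three stronger things, none of which the article supports:

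- **That iron deficiency anaemia would also lose all information.** It would not. It would follow Hb <11 g/dL and be redundant, not empty.
- **That the haematological objective could not be answered.** Anaemia, haemoglobin concentration and continuous ferritin are separate outcomes, and none of them uses the cut-off.
- **That the wrong expansion of AGP worsens the problem.** As an inflammation marker beside CRP, the abbreviation denotes alpha-1-acid glycoprotein. The wrong name appears once, in a list of baseline procedures, and changes no threshold, model or result.

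**Conclusion.** The printed iron-deficiency threshold is wrong by a factor of 1000 relative to 12 ng/mL. The conversion is exact. That practically all children fall below the printed value rests on the assumed ferritin range, but is insensitive to it. That 12 ng/mL is intended is an inference: the evident one from the article's own use of iron deficiency as something that separates children, but not stated there. Taken literally, one secondary outcome loses its contrast, one becomes a duplicate, and a subgroup on this definition has an essentially empty stratum. The primary outcome is unaffected. Severity: a minor correction of a wrong outcome threshold.

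**What to change.** In Secondary outcomes, change the ferritin unit to ng/mL (equivalently µg/L), after confirming the value and unit against the full protocol. Before the blind is broken, check that the analysis plan, the laboratory export and the derivation code for iron deficiency, iron deficiency anaemia and the iron-deficiency subgroup all carry that unit. The expansion of AGP in the baseline section can be corrected at the same time as a separate clerical matter. The cost is a one-word unit change, one name and a short code check. No data collection, sample size or model changes.

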### Detection and reporting of adverse events and serious adverse events

Non-serious adverse events and serious adverse events (SAEs) are collected from the time consent is given until the participant completes the study (the final visit or withdrawal). These are identified through spontaneous reports by the participant, unplanned visits to the research site or any participating health centres, observation by the study staff and standard questioning at each visit (biweekly during the intervention period and monthly during the post-intervention period). All SAEs are reported to the sponsor and the appropriate ethics committee, whether or not they are considered causally related to the investigational products.

### Sample size

The primary objective will be met if either (1) MNPs+DP is superior to DP alone, or (2) iron+DP alone is superior to DP alone or (3) DP alone is superior to placebo on the Bayley-III CogCS immediately after completion of the intervention (midline). A previous study in 2853 Bangladeshi children showed that a 0.2 standardised mean difference (SMD) in Bayley-II Mental Development Index at 7 months translates to a 0.7 SMD at 18 months and a 1.2 SMD at 64 months age.^48^ Therefore, preventing a loss of at least 0.2 SMD may produce magnified long-term developmental benefits as manifestations of brain dysfunction become more evident. A total sample size of 2168 infants (542 per group) will provide 90% power to detect an effect size of 0.25 SMD, assuming a 20% dropout and a two-sided alpha of 1.67% (Bonferroni adjustment for three primary between-group comparisons).

### Statistical analysis plan

A stand-alone statistical analysis plan will be detailed before breaking the blind. This plan will detail all principles and precise methods of analysis, including primary and secondary treatment effects of interest; alternative analyses if model assumptions do not hold; and additional analyses. Participants will be analysed according to their randomised treatment group for efficacy objectives and actual treatment group for safety objectives. The primary outcome of Bayley-III CogCS will be analysed using a mixed-model repeated measures analysis including in the model treatment group, time point and group by time point interaction. The stratification variables sex and site will be included in all models as main effects. In addition, the CREDI variable (collected at baseline) will be included as a main effect in the models for childhood development as it is considered prognostic for childhood development outcomes. Secondary repeated continuous outcomes (eg, growth outcomes) will be analysed similarly to Bayley-III CogCS. The outcome may be appropriately transformed before fitting the analysis model if considered skewed (eg, log-transformation for ferritin). Secondary repeated binary outcomes (eg, haematological outcomes) will be analysed using a log-binomial model and account for the repeated measures with a random intercept for participants. Safety (eg, AEs, infections, hospital attendance) will be summarised during the intervention and post-intervention periods separately and compared between the groups. Analysis of binary repeated outcome safety data (eg, inflammation) and continuous repeated outcome safety data (eg, CRP) will be analysed similarly to the secondary outcomes detailed above. Episode safety data (eg, caregiver reported diarrhoea episodes) will be analysed using negative binomial regression models. Subgroup analyses (eg, sex, site, iron deficiency) will be performed to explore the heterogeneity of the results independent of the study findings.

### Data management

Data collected from the subjects are recorded in digital CRFs using Research Electronic Data Capture (REDCap) software (Vanderbilt University, USA) on tablets. Relevant hard copy patient hospital files are scanned for reference and stored digitally, and securely. The trial is independently monitored by an external monitoring service. No interim analysis is planned.

### Ethics and dissemination

The National Health Science Research Committee, Malawi, and the Walter and Eliza Hall Institute of Medical Research Human Research Ethics Committee, Australia, approved this study. The Malawian Pharmacy and Medicines Regulatory Authority also approved the trial. Additionally, the protocol is registered with the Australian and New Zealand Clinical Trials Registry. Protocol modifications are reported to the ethics committees, regulatory authorities in Malawi, investigators, trial participants and trial registries. Written informed consent in the local language (see online supplemental file 3) is obtained from each participant’s parent/legal guardian before conducting any study-related procedure. In the event where the participant’s parent/legal guardian is illiterate, the informed consent form is read out loudly to the potential participant’s parent/legal guardian in the presence of an impartial witness. The potential participant’s parent/legal guardian thumbprints the consent form if they agree to participate in the study and the witness signs to indicate he/she witnessed the whole consenting process. The results will be presented and shared with the local community that hosted the research and to the international forum. We will publish in peer-reviewed scientific journals and report to relevant policymaking bodies like the Malawi Ministry of Health.

10.1136/bmjopen-2022-069011.supp3Supplementary data

